### Interim analyses {21b}

Three interim analyses are planned:Interim analysis I will be conducted after the pilot phase for safety assessment of the 6 weeks’ results of part A subjects. All AEs of the safety population will be summarized for the analysis. Where applicable, descriptive statistics may be used based on AE categories. No analysis of the primary endpoint, secondary performance, or other variables will be performed.Interim analysis II is planned for the purpose of sample size re-estimation. The sample size re-estimation will be performed if either the first 134 patients have passed their 12-month follow-up time point or when more than 90% of the subjects of the initially calculated sample size (242 or more subjects) have been treated, whatever happens first. The interim analysis is performed based on unblinded data, because the effect size and the events in the control group cannot be reliably predicted. No confirmatory test is carried out during interim analysis II (i.e., no early efficacy or futility stop).The interim analysis III includes analyses of primary and secondary efficacy endpoints, based on the intention-to-treat population. The primary endpoint analysis will be conducted as soon as the 12-month follow-up period of the stage 2 patients is completed.

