### Trial design {8}

This clinical investigation is a parallel-group, randomized, controlled trial with a 1:1 allocation ratio following a superiority framework. This clinical investigation consists of two stages: pilot stage (part A) and pivotal stage (part B).

The two stages of the clinical investigation allow an early assessment of short-term safety of the investigational products at the beginning (part A) with a low number of subjects. This is followed by the main clinical investigation (part B). In addition, an adaptive study design allows the extension of the sample size at interim analysis during part B.

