### Outcomes {12}

The primary endpoint is the infection-free survival rate, evaluated to demonstrate that revision hip implants with the antimicrobial silver coating significantly reduce the rate of periprosthetic reinfections within 12 months after hip revision arthroplasty. The primary variable is the occurrence of periprosthetic joint infection classified as “infection likely” or “infection confirmed” according to the European Bone and Joint Infection Society (EBJIS) criteria [11]. The time point for assessing this outcome is 12 months postoperatively, as the silver coating is designed to provide efficacy within this period. 

Secondary endpoints will be functional outcomes assessed using the Harris Hip Score (HHS) [14], focusing on pre- and postoperative scores to determine improvements in hip functionality, as well as quality of life evaluated through the EQ-5D-5L questionnaire [15]. Further, Kaplan-Meier implant survival will be determined for endpoints including septic revisions and all-cause revisions. Radiological outcome (hip stem migration, radiological signs of loosening, radiologic observations in the fixation area) will be evaluated using standardized X-rays. Safety outcomes including device failure, signs of systemic or local argyria, and (S)AEs and (S)ADEs will be documented. In addition, specific laboratory parameters related to liver (ALT, AST, GGT) and kidney (eGFR) function, as well as inflammatory markers (e.g., CRP, leukocytes), silver ion in peripheral blood and drainage liquid, and surgery-related data, including bone defect classification, length of stay, and antibiotic therapy details will be evaluated.

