**Fig. 1 Fig1:**
[figure not shown]
Planned study visits

**Table 1 Tab1:** Participant timeline: schedule of enrollment, interventions, and assessments

		Post-randomization			Follow-Up			
Timepoint	*−**7 to **−**2*	0	*1 to 3 days*	*2 weeks*	*6 weeks*	*6 months*	*12** months*	*24** months*
Enrollment								
Eligibility screen	X							
Informed consent	X							
Randomization	X							
Intervention/comparator								
*IP-coated device*		X						
*Non-IP-coated device*		X						
Assessments								
*Infection-free implant survival rate (signs of required revision)*			X	X	X	X	X	X
*Harris-Hip-Score, Eq-5D-5L*	X		X	X	X	X	X	X
*Radiological outcome (hip stem migration, signs of loosening, fixation) *via* X-rays*		X		X			X	X
*Safety (laboratory blood parameter, signs of systemic or local argyria, (S)AEs/(S)ADE, device failure)*			X	X	X	X	X	X

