### Sample size {14}

The sample size calculation for this study is based on the 1-year event rate of PJI in the comparator group, assumed to be 21.5%. This assumption is derived from a custom analysis of the EPRD (German Arthroplasty Registry) data [1], which documents revision procedures where implant components are exchanged, including Kaplan–Meier estimates for re-revision rates (total, infection related, and non-infection related) at 6, 12, and 24 months. Specifically, the re-revision rate due to periprosthetic infection within 12 months, for procedures involving combined exchange of stem and cup, was reported as 16.4%. However, this figure only accounts for cases where reinfections resulted in implant exchange and does not fully capture all events classified under the EBJIS criteria (“infection likely” or “infection confirmed”). To address this, a correction factor of 1.33 was applied to account for cases of reinfection treated with alternative approaches, such as antibiotic suppression therapy, implant retention surgery (DAIR), amputation, or where infection was not documented at the time of registry entry. After this adjustment, the estimated event rate in the comparator group increased to 21.5%.

In the intervention group, the event rate is assumed to be 8.6%, reflecting an anticipated 60% reduction in the rate of periprosthetic reinfections. The effect size estimation is based on the estimated reduction of periprosthetic infections in humans by 90% (unpublished case series), a reduction of periprosthetic infections in a rabbit model by 65% [16], and a reduction of infections in canine osteosynthesis implants by 73% (unpublished manufacturer data) or by 39% in the same canine implant type based on a different study [17].

Using a one-sided chi-square test for independent two-sample proportions with a significance level of *α* = 0.025 and a power of 80%, the study requires 240 participants (120 per group) to meet the primary endpoint. To account for a 10% drop-out rate, a total of 268 patients will be enrolled, with 20 patients allocated to part A and 248 patients to part B. Sample size was calculated using SAS (SAS VIYA software version V.04.00, SAS Institute Inc., Cary, NC, USA).

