The above chi-squared based sample size calculation was used, although log-rank tests are used for primary hypothesis tests. A comprehensive simulation-based sample size calculation using the log-rank statistics under variation of the underlying hazard function found a small to marginal increase in power compared to the chi-squared statistic.

As predefined in the protocol, an extension of the total sample size of up to 50% is allowed, which results in a maximum of 400 patients (360 patients + 10% dropout). The 50% limit was determined based on practical considerations. This results in 20 patients scheduled for the safety phase (part A) and up to 380 patients scheduled for the main phase (part B).

The sample size re-estimation will be based on all available data of the first 134 treated patients, limited to their 12 months follow-up visit (“right truncated”). By estimating the per-group hazard, based on the corresponding survival data, the conditional power for detecting the difference in primary outcome between the two groups in the final analysis will be re-estimated. Details can be found in Wassmer and Brannath [18]. In case the intended number of 268 study subjects yields a conditional power smaller than 80% for the log-rank test in the final primary analysis, the number of subjects to be included in the study is increased up to the prespecified limit of 400 patients. When the conditional power based on the initially planned 268 patients is 80% or above, the clinical investigation will continue using the planned sample size. If the conditional power is very small (e.g. < 10%), the study will be completed with the originally estimated sample size.

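### Interim analysis I, the 6-week safety review of part A, is limited to adverse events and, read literally, leaves out laboratory, argyria and device-failure data that the protocol itself classes as safety

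*Protocol article*

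**What the plan says.** Under Trial design {8}, the protocol article says that the two stages "allow an early assessment of short-term safety of the investigational products at the beginning (part A) with a low number of subjects", with the main investigation (part B) to follow.

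Under Interim analyses {21b}: "Interim analysis I will be conducted after the pilot phase for safety assessment of the 6 weeks’ results of part A subjects". The content is then set as a summary of adverse events in the safety population, with optional descriptive statistics by adverse-event category. The description closes with the exclusion: "No analysis of the primary endpoint, secondary performance, or other variables will be performed".

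Two other places describe what safety data the trial collects:

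- The safety row of Table 1 reads "Safety (laboratory blood parameter, signs of systemic or local argyria, (S)AEs/(S)ADE, device failure" and is marked at days 1 to 3, week 2 and week 6, and at the later visits.
- Outcomes {12} names device failure, argyria and adverse events or device effects as safety outcomes. It then lists ALT, AST, GGT, eGFR and inflammatory markers, and "silver ion in peripheral blood and drainage liquid, and surgery-related data".

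The statistical methods section plans a descriptive analysis of silver concentrations but ties it to no interim analysis. The oversight sections give the DMC a continuing safety role and leave its duties and procedures to a charter.

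**The concern.** The review is introduced as a safety assessment of the 6-week results, yet its content is narrower than the protocol's own account of safety. This is a stated exclusion. It is not a detail left for the statistical analysis plan: a plan written to follow the sentence literally could not add laboratory or silver tables at this point.

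The device works by releasing silver ions. A shift in liver or kidney values, or a raised silver concentration, need not have been reported as an adverse event by week 6. If it was not, the only pre-specified look at part A could be completed without showing it, although at least the laboratory values are scheduled to have been collected. With so few exposed patients, it makes little sense to set aside safety information that is already in hand.

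**Working it through.** **1. Setting the passages side by side.** The safety row of Table 1 has four components.

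| Component in Table 1 | Scheduled by week 6 | Named as content of interim analysis I |
|---|---|---|
| Laboratory blood values | Days 1–3, week 2, week 6 | No |
| Argyria, local or systemic | Days 1–3, week 2, week 6 | No |
| Adverse events and device effects | Days 1–3, week 2, week 6 | Yes |
| Device failure | Days 1–3, week 2, week 6 | No |

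One of four is retained. The statistical methods section also lists device failure and component revision separately from adverse events when it describes the safety analyses, so the protocol does not treat them as the same thing.

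Silver is less clear. Outcomes {12} lists it, but neither that section nor Table 1 gives sampling times. That silver values exist by week 6 is therefore an inference. That liver and kidney values exist by week 6 is better supported, because Table 1 schedules laboratory blood values then.

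**2. The plan's own totals.** From Sample size {14}: "a total of 268 patients will be enrolled, with 20 patients allocated to part A and 248 patients to part B". The totals reproduce:

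- Planned: 240 / 0.90 = 266.7, so 267, or 268 when rounded up to equal arms; 20 + 248 = 268.
- Maximum: 360 / 0.90 = 400; 20 + 380 = 400.

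**3. Coated recipients.** The trial is a "parallel-group, randomized, controlled trial with a 1:1 allocation ratio", so half of each part receives the coated implant:

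- Part A: 20 / 2 = 10.
- Part B as planned: 248 / 2 = 124.
- Part B at the maximum: 380 / 2 = 190.

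The split within part A is approximate, because randomisation uses site-specific lists with random block sizes.

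**4. What an adverse-event count in 10 patients can show.**

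- Zero events of a given kind in 10: the one-sided 95% upper bound solves (1 − p)^10 = 0.05, so p = 1 − 0.05^(1/10) = 0.259, or 25.9%.
- A true risk of 10% produces no event at all with probability 0.9^10 = 0.349, about 35%. The chance of at least one event is about 65%.

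Both figures follow from n = 10 whatever is tabulated. They show that a clean adverse-event summary is weak reassurance. They do not measure how much the extra tables would add, and the article gives no variances or thresholds from which that could be calculated.

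**The case against.** The strongest reply is that the sentence limits one statistical report and not what the DMC may see. The oversight sections let the DMC review safety data throughout, advise on continuation and recommend early termination, with no restriction to adverse events. The tables it receives may be set out in the charter, which is not shown. A reader might infer from the exclusion that the DMC would never see laboratory or silver data, or that such data cannot influence the move to part B. The documents do not support that. What remains is that the one review pre-specified for part A excludes these data, and the article nowhere says that they reach the DMC by another route.

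Second, the phrase about other variables ends a list that begins with efficacy and performance, so it may have been meant as other non-safety variables. That reading is possible, but nothing in the section exempts non-adverse-event safety data. If it is what the sponsor intended, the sentence still needs rewording.

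Third, the adverse-event section requires everything mentioned by the patient or observed by the investigator to be reported, together with device deficiencies. Laboratory changes or argyria judged to be adverse events would therefore appear in the summary. This stands. It does not cover shifts that nobody reports as an event, and the article does not say which laboratory values count.

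Fourth, a reader might take part A as a formal barrier with a release rule. The article says only that part B follows part A. It states no go/no-go criterion and no enrolment pause.

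**Conclusion.** The point holds as a conflict between the stated purpose of part A and Table 1 on one side and the content of interim analysis I on the other. Taken literally, three of the four safety components scheduled through week 6, and any silver concentrations available by then, fall outside the only pre-specified part A review. That review rests on about 10 coated recipients and comes before about 124 planned in part B.

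It would be tempting to describe the step as one from 10 to 200 coated patients. That overstates it. The figure of 200 is half of the 400 maximum and includes part A, and the 190 in part B is reached only if the sample size is extended after interim analysis II, on a DMC recommendation that must take the risk–benefit profile into account.

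The conclusion assumes the literal reading of the exclusion, an even split in part A, and no separate provision in the charter. It is a correction that should be made for the quality of the safety review. It does not affect the validity of the primary analysis.

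**What to change.** Under Interim analyses {21b}:

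- Keep the bar on the primary endpoint and on performance endpoints, and narrow its last element to other non-safety variables.
- State that the DMC receives, with the adverse events, descriptive summaries by implant group of laboratory safety values (including ALT, AST, GGT and eGFR), argyria findings, device failures and any silver concentrations available to week 6.
- Reconcile this wording with Trial design {8}, Table 1 and the DMC section. If the charter already provides for these data, a cross-reference is enough.

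The cost is a few descriptive tables and timely laboratory reporting, chiefly for silver. There is no type I error cost, because the primary endpoint stays closed. Supplying the same tables at interim analysis II would be a sensible optional addition. The first patient was treated in June 2025, so it would be of more use if interim analysis I has already taken place.

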### Methods for additional analyses (e.g., subgroup analyses) {20b}

Subgroup analyses will explore outcomes stratified by patient factors such as surgical treatment (one-stage vs. two-stage revision), infection severity, and baseline functional status. Adjusted analyses may be conducted using multivariable regression models to account for potential confounders (e.g., age, comorbidities, and ASA physical status).

### Methods in analysis to handle protocol nonadherence and any statistical methods to handle missing data {20c}

The primary analysis will follow the intent-to-treat (ITT) principle, including all eligible randomized participants in the groups they were assigned. A per-protocol (PP) analysis will be conducted as a sensitivity analysis, excluding participants with significant protocol deviations.

Statistical methods (e.g., multiple imputation) for handling missing values are not used. In the case of a partial date such as adverse event onset date or date of death, the unknown portion of the date of the event will be imputed. If the month and year are known, the 15th of the month will be used for analysis. If only the year is known, the event will be analyzed as if it occurred on June 30 of the known year. In the rare case that the date is fully unknown, the date will be imputed as the operation date.

Dropout reasons will be carefully documented to assess potential biases.

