## Statistical methods

### Statistical methods for primary and secondary outcomes {20a}

The primary endpoint of this study is the comparison of infection-free survival rates (periprosthetic infections) within 12 months after revision total hip arthroplasty (THA) due to periprosthetic joint infection. The following hypothesis will be tested:H₀ (null hypothesis): hT ≥ hCHₐ (alternative hypothesis): hT < hC

where hT represents the hazard function in the treatment group and hC represents the hazard function in the control group for the 12-month postoperative period.

The primary null hypothesis is tested using a one-tailed inverse normal combination test at *α* = 0.025, allowing for a two-stage adaptive study design that combines log-rank tests for each stage. The null hypothesis is rejected if the combined *p* < 0.025. The *p*-values for each stage (*p*₁ and *p*₂) will be calculated using a one-sided log-rank test for periprosthetic reinfections (as defined by EBJIS criteria) within 12 months post-treatment. Kaplan–Meier survival curves will be right-censored at 12 months.

Descriptive statistics or comparative analyses between the treatment and control groups for demographic data, safety, and performance variables will be conducted where appropriate. Functional outcome and quality of life in the treatment groups between treatment arms will be evaluated using a linear regression model with repeated measures. Two-year implant survival will be evaluated according to the Kaplan-Meier method and compared in the treatment arms with log-rank test for the events periprosthetic joint infections, septic revisions, and all-cause revisions. Occurrence of any radiolucent line, and occurrence of hip stem migration > 2 mm will be analyzed by using a logistic regression model with repeated measures, as well as the mean migration in patients with relevant migration (> 2 mm) by using a linear regression model with repeated measures. Safety outcomes of adverse events, device failure, and component revision between treatment arms will be evaluated by using a logistic regression.

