## Trial status

The first patient was treated on 25 June 2025, and last patient’s last visit is expected for Q3 2028. Protocol version is 5.0, 21 March 2025.

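### The partial-date rules have no bounds, so they can date a postoperative event before surgery, on the day of surgery or beyond the 12-month window

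*Protocol article*

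**What the plan says.** The rules stand in the protocol article under the heading on protocol nonadherence and missing data {20c}. Their scope is set by the opening words, "In the case of a partial date such as adverse event onset date or date of death, the unknown portion of the date of the", after which the sentence provides for filling in the missing part. Three defaults follow:

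- Month and year known: "If the month and year are known, the 15th of the month will be used for analysis".
- Only the year known: "If only the year is known, the event will be analyzed as if it occurred on June 30 of the known year".
- Nothing known: "In the rare case that the date is fully unknown, the date will be imputed as the operation date".

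The same section excludes other approaches: "Statistical methods (e.g., multiple imputation) for handling missing values are not used". It states no limit at the operation date, at the last visit without the event or at the record that first shows it, and it has no separate rule for reinfection dates.

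The primary analysis is time to event. Under the statistical methods {20a}, each stage's p-value "will be calculated using a one-sided log-rank test for periprosthetic reinfections (as defined by EBJIS criteria) within 12 months post-treatment", and "Kaplan–Meier survival curves will be right-censored at 12 months". The Trial status section says: "The first patient was treated on 25 June 2025".

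**The concern.** A default date is acceptable only if it falls where the event could have happened. Here the defaults are tied to the calendar, while the analysis counts days from surgery. A mid-year default precedes surgery for anyone operated on in the second half of a year who has an event in that same year. A mid-month default does so for anyone operated on after the 15th who has an event later that month. For an event in the calendar year after surgery, 30 June can instead fall beyond 12 months. The default for a wholly unknown date puts the event at day 0 even when later visits recorded no infection.

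Adverse event onset and death are given only as examples, so the wording also covers a reinfection date. Two outputs are exposed: the primary log-rank comparison, and the adverse event summaries, where a postoperative event could be counted as preoperative. The article does not say what happens to a negative time. That choice would then be made during the trial, in a study where surgeons know the implant type and interim analysis II uses unblinded data.

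**Working it through.** **Inputs.** The three defaults ({20c}); first treatment on 25 June 2025 and last visit expected in Q3 2028 (Trial status); 12-month primary window ({20a}); planned event rates of 21.5% and 8.6% with 120 per group (Sample size). Assumed, because the article does not give them: operations spread evenly from 25 June 2025 to 30 September 2026 (end of Q3 2028 minus the 24-month follow-up), and event times uniform over days 1-365 or over days 1-90.

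**The plan's own figure.** There is none for partial dates. The planned size is reproduced: a pooled chi-square test at one-sided 0.025 with 120 per group has 80.2% power. Expected primary events are 120 × 0.215 + 120 × 0.086 = 25.8 + 10.3, about 36.

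**Single cases** (day = imputed date minus operation date):

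| Operation | What is known | Imputed date | Day |
|---|---|---|---|
| 10 Oct 2025 | 2025 | 30 Jun 2025 | -102 |
| 20 Sep 2025 | Sep 2025 | 15 Sep 2025 | -5 |
| 25 Jun 2025 (first patient) | Jun 2025 | 15 Jun 2025 | -10 |
| 1 Mar 2026, true event 10 Jan 2027 (day 315) | 2027 | 30 Jun 2027 | 486 |
| any | nothing | operation date | 0 |

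**Shares.** Each default was applied to every operation day and every event day in the assumed window:

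| Share of imputed dates | Events over days 1-365 | Events over days 1-90 |
|---|---|---|
| Year-only, before surgery | 17.4% | 49.8% |
| Year-only, after day 365 | 10.2% | 0% |
| Month known, before surgery | 1.0% | 4.1% |

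If operations end on 1 July 2026 instead, the year-only shares before surgery are 12.5% and 37.5%, and the share after day 365 is 12.7% for events over days 1-365. Year-only events that occurred in 2025 are dated before surgery in about 94-96% of cases, because hardly any operations took place between 25 and 30 June.

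These are shares of dates that are already partial. They cannot be turned into an expected number of affected events, because the frequency of partial dates is not given.

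**Effect on the primary test, per affected event.**

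- *If an event were lost.* With HR = ln(0.914)/ln(0.785) = 0.371, Schoenfeld power is 84.4% with 36 events, 83.4% with 35 and 82.3% with 34: about one point per event. With 26 control and 10 intervention events, a one-sided two-proportion test gives p = 0.0019; with one control event fewer (25 vs 10), p = 0.0030.
- *If an event is set to day 0.* It still counts. Over 300 simulated trials with uniform event times, moving one control event to day 0 changed the mean log-rank z from 2.89 to 2.90 for 26 vs 10 events, and from 1.96 to 1.97 for 24 vs 13. No single shift exceeded 0.02.

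**The case against.** The strongest objection is that the rules will rarely touch a primary event. Table 1 schedules infection assessment at 1-3 days, 2 weeks, 6 weeks, and 6, 12 and 24 months, so an EBJIS-classified infection known only by its year is unlikely, and the article calls the fully unknown case rare. The data management section provides for plausibility checks and queries, which should catch an event dated before surgery. A limit at surgery could also be seen as a detail for the analysis plan. The points on frequency and checking stand, and they keep this minor. The last does not: the article prints complete rules, and those rules give impossible dates. A query also cannot settle a date that the site does not know.

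A reader might infer three stronger things that the documents do not support.

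- *That primary events will be dropped.* The article does not say how negative times are handled.
- *That one lost event could decide the trial.* With 24 vs 13 events, p = 0.0246, and losing a control event gives 23 vs 13 and p = 0.035. But that result is chosen to sit at the boundary. Losing an intervention event instead (24 vs 12) gives p = 0.015, and the rules are the same in both arms.
- *That an unknown death date erases a patient's infection-free follow-up.* This requires infection follow-up to be censored at death, and the article does not state how deaths are handled.

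**Conclusion.** Wrong as written, and minor. The unbounded defaults can place a postoperative event before surgery, at day 0 or past day 365. The calendar examples need no assumption beyond the printed rules and the start date; the percentages depend on the assumed spread of operations and event times. The rules can reach the primary analysis, but the number of partial dates is unknown and the effect on the primary test is probably small. Planned sample size and design are unaffected.

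**What to change.** Keep the 15th and 30 June as defaults, and add limits. An imputed date may be no earlier than the later of the operation date and the last visit documented as event-free, and no later than the first record of the event. For a fully unknown date, impute within the same interval instead of using the operation date. State that the rule applies to reinfection dates. Whatever rule is used for deaths, add that a partly or fully unknown death date must not shorten documented infection-free follow-up. A particular method such as the interval midpoint is one option, but the defect does not require it.

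Make the change before the unblinded interim analysis II. It costs one paragraph in the protocol and analysis plan and a few lines of code, with no effect on sample size or patient care.
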